### Data management {19}

Data collection forms transferred to/from the CTRU will be coded with a study number (made up of the recruitment site code and the participant’s unique sequential trial number), the participant’s initials, and date of birth. Study data will be held securely on paper and electronically at the University of Leeds’ CTRU, and appropriate processes put in place for the transfer, storage, restricted access, and disposal of personal information. Relevant Standard Operating Procedures, Guidelines and Work Instructions in relation to data management, processing, and analysis of data will be followed.

### Confidentiality {27}

All study staff and investigators will endeavour to protect the rights of the trial’s participants to privacy and informed consent. All information collected will be handled strictly in accordance with the consent provided, adhering to the Data Protection Act 2018 [52] at all times. Upon study completion, sites will archive all study data until authorisation for confidential destruction is provided by the study sponsor. Upon study completion, the data shall be transferred from CTRU to the University of Nottingham in an encrypted format and stored for at least 7 years. The Trial Master File and documents held by the CTRU will be archived at secure facilities at the University of Nottingham and University of Leeds.

### Plans for collection, laboratory evaluation, and storage of biological specimens for genetic or molecular analysis in this trial/future use {33}

There are no plans for collection, laboratory evaluation, or storage of biological specimens for this study.

### Interim analyses {21b}

No interim analyses are planned.

### Methods for additional analyses (e.g. subgroup analyses) {20b}

Baseline characteristics of those lost to follow-up will be compared with those not lost to follow-up to assess for bias. In addition to the intention to treat (ITT) analysis, Complier Average Causal Effect (CACE) analyses will be undertaken on the primary endpoint in order to measure the impact of the intervention among participants who complied with treatment. Parameter estimates for the intervention effect can then be compared with those from the ITT analysis to help better evaluate the effect of the intervention. Several CACE models will be examined, using increasingly strict definitions of engagement. The CACE models will use the same mixed-effects modelling techniques used in the primary analysis to ensure for reasonable comparisons to be made. Baseline characteristics of those lost to follow-up at the 12-month timepoint will be compared with those not lost to follow-up to assess for bias.

### Methods for economic analysis

A within-trial economic evaluation (a cost-utility analysis) will be conducted comparing the costs and QALYs in the ESSVR plus usual care group to usual care alone group for participants of working age from the perspective of the UK NHS and PSS in the base case as recommended [53] and from a wider perspective in secondary analysis to reflect the expected wider costs and benefits of the VR intervention.

The intervention resource use (comprising training, mentoring, and delivery) will be captured and recorded by the intervention OTs. This will be used to estimate the cost of the training and mentoring components to be used in the main economic evaluation. Levels of wider health, PSS, and societal resource use at baseline, 3, 6, and 12 months will be captured using a bespoke resource use questionnaire designed for self-completion (or with help where required). Although intervention delivery costs will be estimated using data captured by the OTs delivering the interventions, these will not be included in the economic evaluation as it was felt by the research team, which includes PPI members, that participants would not be able to distinguish between intervention OT visits and non-intervention OT visits such that participants are going to be asked explicitly to include all visits in their responses to the resource use questions. To avoid the potential for double counting, we will therefore base resource use and costs on patient reported data only with the exception of training and mentoring costs. We will attach published national unit costs using the common recent price year [54–56] to individual-level quantities of resource use and estimate the mean cost per participant incorporating the cost of the intervention and wider healthcare and PSS resource use (primary care, secondary care, emergency care, medications, and social services). Secondary analysis will take a wider cost perspective including participants, carers, and employers and wider public sector services perspective where possible.

Health-related quality of life will be measured using the EQ-5D-5L [47, 57] at baseline, 3, 6, and 12 months, and valued in line with guidance at the time of analysis [58]. QALYs will be estimated for the trial period using linear interpolation and area under the curve analysis, adjusting for baseline values [59].

A regression-based approach (seemingly unrelated regression equations) [60] will be used for the statistical analysis if the necessary assumptions hold. The level of uncertainty associated with the decision over which option is most cost-effective will be explored using non-parametric bootstrapping [61] to construct the cost-effectiveness acceptability curve (CEAC) [62]. Neither costs nor QALYs will be discounted reflecting the time frame of the trial. Missing data will be handled in line with the approach reported by [63]. Where appropriate, the economic analysis will take the same approach to missing data as the clinical statistical analysis to ensure consistency. Sensitivity analysis will explore the impact of different ways of handling missing data.

The planned economic analysis is subject to change to ensure it stays in line with any changes to accepted methodology during the course of the study. A detailed Health Economics Analysis Plan will be finalised and reviewed by an independent health economist prior to the trial database being locked.

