### Intervention description {11a}

#### ESSVR (plus UC)

ESSVR is an early, individually tailored intervention delivered by stroke specialist OTs who have undergone training delivered by experienced OTs from the central RETAKE team during site set-up. The 2-day face-to-face training package includes provision of an ESSVR manual, clinical scenarios, and case studies to support learning for the delivery of ESSVR. The RETAKE OTs will be briefed via group discussion and case studies on the trial’s design, paperwork to be completed, and issues relating to delivery of the intervention within the trial context. Throughout the study duration, RETAKE OTs will receive a 1-day refresher training day, monthly group mentoring sessions, and ad hoc individualised support via email or telephone.

RETAKE OTs will initiate communication with ESSVR participants via telephone or letter. The content, dose (e.g. number of sessions), intensity, and duration of the intervention will be individually tailored according to participants’ needs, their preferences, and employment context.

RETAKE OTs will follow the ESSVR manual and record delivery of content, duration, and dose on Case Reporting Forms (CRFs) and routine treatment records. Assessments and intervention will include the following:
Assessing the impact of stroke on the participant and their jobEducating patients, employers, and families about stroke impact on workFinding strategies to lessen impact, e.g. memory aids, pacing to conserve energyWork preparation, including establishment of routines and opportunities to practice work skills (e.g. use of computers to increase concentration, walking to increase physical stamina)Liaison with employers and employment advisors to plan and monitor a phased RTW (as needed for up to 12 months post-randomisation)

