The National Stroke Strategy [18] and National Institute of Health and Care Excellence (NICE) [19] both recommend that VR be offered to stroke survivors in a timely manner to enable reasonable and necessary adjustments to be made to support their RTW. NICE recommends identifying the demands of the working role and the person’s impairments on work performance, tailoring the VR intervention, educating employers about the Equality Act 2010 and support available, conducting workplace visits, and liaising with employers to establish reasonable accommodations such as phased return or equipment provision [19]. The ESSVR intervention incorporates all of the above recommendations, but also includes consideration of adjustments that can be made to work roles/responsibilities, levels of supervision and support, work preparation activities, and education for stroke survivors, employers/co-workers, and families about stroke-specific disabilities.

The lack of an approved VR pathway within local areas has previously resulted in miscommunication, inadequate training and knowledge of stroke and VR, poor cross-service collaboration, and mild stroke patients receiving little or no support to RTW [66]. The ESSVR intervention is innovative because it encourages collaboration across the workplace and acute and community health services, an approach highly recommended in the aftermath of the COVID-19 pandemic [67]. Occupational therapists delivering the intervention are specially trained to meet the needs of stroke survivors wishing to RTW and encouraged to provide a flexible and responsive service for as long as necessary up to 12 months post-stroke. Individually tailored cross-service interventions of this kind can be more costly in the short-term. However, a pilot study for a similar intervention among people with traumatic brain injuries reported that the mean health costs per person were only £75 greater per annum [68]. In addition, the long-term cost benefits for this intervention could be high. The 6-year follow-up (19 out of 43 participants) for the feasibility RCT demonstrated that most stroke survivors working at 12 months were still working 6 years later (74%; *n* = 14) [37]. People who return to and stay in work contribute more to the economy and are less likely to experience and require expensive treatment for depression [32, 69].

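### ESSVR work done without the participant has no stated route into the economic evaluation, so incremental cost is likely understated

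*Protocol article*

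**What the plan says.** All of the costing rules are in the Protocol article, Methods for economic analysis. The intervention therapists (OTs) record the resources used in training, mentoring and delivery. The delivery part is then set aside: "intervention delivery costs will be estimated using data captured by the OTs delivering the interventions, these will not be included in the economic evaluation".

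The reason is that participants are not expected to be able to tell ESSVR visits from other OT visits. So "participants are going to be asked explicitly to include all visits in their responses to the resource use questions", and adding the OT records on top would count ESSVR visits twice. The rule that follows is: "we will therefore base resource use and costs on patient reported data only with the exception of training and mentoring costs". A later sentence in the same section says the analysis will "estimate the mean cost per participant incorporating the cost of the intervention" and wider care.

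Intervention description {11a} lists, as part of ESSVR, "Liaison with employers and employment advisors to plan and monitor a phased RTW" for up to 12 months, together with education of employers. Background and rationale {6a} describes ESSVR as including case coordination. OTs log the content, duration and dose of delivery on case report forms and treatment records.

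The one sensitivity analysis stated for the economic evaluation concerns missing data. None using the OT delivery records is stated.

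**The concern.** The questionnaire asks participants about visits. Some of what an ESSVR therapist does is not a visit to the participant: speaking with an employer or employment advisor, educating a workplace, coordinating the case, travelling. Participants cannot report as their own visits work at which they were not present. This is therapist time, it belongs in the NHS and PSS base case, and the usual-care-alone arm has no ESSVR equivalent of it. A cost that falls in one arm and is left out lowers the incremental cost.

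Cost-effectiveness is part of the stated aim and one of the secondary objectives, and the article says favourable evidence would support NHS roll-out. An incremental cost that is too low would make that evidence look stronger than it is.

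**Working it through.** **1. Where each component enters the costs** (Protocol article: Study setting {9}, Intervention description {11a}, Methods for economic analysis)

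| Component | Arm | Route into costs |
|---|---|---|
| Training and mentoring | ESSVR | OT records |
| ESSVR visits to the participant | ESSVR | Questionnaire |
| Calls, emails, texts to the participant | ESSVR | Possibly questionnaire (not shown) |
| Employer and advisor liaison and education, case coordination, any recorded travel | ESSVR | None stated |
| Other OT and wider care | Both | Questionnaire |

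**2. Error in incremental cost.** Per ESSVR participant, let V be the cost of ESSVR contact with the participant, N the cost of ESSVR work without the participant, and D = V + N. Let Δ be the between-arm difference in other reported OT care, and c the share of contact cost that self-report captures, taken as equal in both arms.

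- True difference: V + N + Δ
- Difference under the plan: c(V + Δ)
- Understatement: N + (1 − c)(V + Δ)

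With perfect recall (c = 1) the understatement is still N. That term is structural. The second term is recall error and can take either sign.

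**3. Illustration.** The article gives no delivery cost, unit cost or QALY gain, so there is no stated figure to reproduce and everything here is assumed. Setting Δ = 0 and r = cV/D (the share of delivery cost captured), the understatement is (1 − r) × D:

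| D | r = 0.5 | r = 0.7 | r = 0.9 | r = 1.0 | r = 1.1 |
|---|---|---|---|---|---|
| £500 | £250 | £150 | £50 | £0 | −£50 |
| £1,000 | £500 | £300 | £100 | £0 | −£100 |
| £2,000 | £1,000 | £600 | £200 | £0 | −£200 |

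The cost-effectiveness ratio (ICER) shifts by (1 − r) × D / QALY gain. At r = 0.7 and an assumed gain of 0.02 to 0.05:

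- D = £1,000: £300/0.02 = £15,000 down to £300/0.05 = £6,000 per QALY too low.
- D = £500: £7,500 to £3,000.
- D = £2,000: £30,000 to £12,000.

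**4. What would cancel it.** If N is a share s of D, reported contact must be inflated to c = 1/(1 − s) to offset the omission. For s = 0.1, c = 1.11; for s = 0.3, c = 1.43; for s = 0.5, c = 2.0. A small omission could be hidden by modest over-reporting; a large one is unlikely to be.

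**5. Can overlap be removed by subtraction?** With E ESSVR contacts recorded by the OT and R OT contacts reported by the participant, subtraction floored at zero gives E + max(0, R − E) = max(R, E).

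- E = 10, 5 other OT contacts, 70% recalled: R = 0.7 × 15 = 10.5, netted total 10.5. Nothing changes.
- Same contacts, 60% recalled: R = 9, netted total 10. All 5 other OT contacts vanish, and this can happen in the ESSVR arm only.

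So subtraction does little for contact with the participant. For N there is no overlap to remove.

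**The case against.** The plan replaces one data source with another for a stated reason, reached with patient and public input. ESSVR visits are costed through the questionnaire, and training and mentoring through OT records. The published unit costs may already spread non-contact time over contact time, in which case part of N is paid for. The questionnaire is not shown, may ask about remote contact, and can be completed with help. The article calls the economic analysis subject to change and promises a detailed, independently reviewed Health Economics Analysis Plan before database lock.

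Much of this stands and rules out stronger readings that a reader might infer:

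- **That ESSVR delivery goes uncosted.** It does not; contact with the participant enters by self-report.
- **That recall error and non-response bias one arm only.** Both affect both arms, and unreturned questionnaires are handled as missing data, not as zero cost.
- **That the ICER is certain to be too low.** Over-reporting, misclassified visits or loaded unit costs could offset the omission.
- **That the article contradicts itself.** The sentence on including the intervention's cost is compatible with self-reported visits plus training and mentoring.
- **That the shortfall is a multiple of the £75 in the Discussion.** That figure ("the mean health costs per person were only £75 greater per annum") is a difference in mean health costs from a traumatic brain injury pilot, not a delivery cost.

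What the objection does not answer is the work done without the participant. The exclusion is an explicit rule, not a detail left open, and double counting is no reason for excluding that work.

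**Conclusion.** The concern holds for ESSVR work done without the participant. As the costing rule is written, that work has no route into the costs and falls in one arm, so incremental cost is likely understated and the ICER and acceptability curve are likely too favourable. The direction rests on two assumptions: that such work is more than trivial, and that neither over-reported visits nor the chosen unit cost makes up for it. The article does not give the size; the amounts in the working show scale only. The point concerns the economic objective, which is secondary, and leaves the primary return-to-work comparison untouched. It should be corrected, and it can be, because delivery costs are to be estimated from OT records in any case.

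**What to change.** In the Health Economics Analysis Plan, before database lock:

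1. **Base case:** add OT-recorded ESSVR time spent without the participant (liaison, employer education, case coordination, any recorded travel) to the patient-reported costs. Use a unit cost that does not already load non-contact time onto contact time; otherwise this work would be counted twice. First confirm that the OT records separate time with the participant from time without, since the article says only that content, duration and dose are logged.
2. **Sensitivity analysis:** cost all ESSVR delivery from OT records, with a stated rule for overlap with self-reported OT contacts. If the rule is subtraction floored at zero, say that it yields the larger of the two counts and can remove other OT contacts in the ESSVR arm.
3. **Comparison scenario:** keep the patient-report-only costing.
4. **Wording:** state which components make up the cost of the intervention.

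The cost is analysis-plan text and some data linkage, with no new data collection provided the records make the split in item 1. The downsides are an overlap rule that is only approximate and, probably, a less favourable ICER.

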### Methods in analysis to handle protocol non-adherence and any statistical methods to handle missing data {20c}

Analyses will be conducted on all randomised participants, in the study arms to which they were allocated, regardless of intervention non-adherence. Missing data may occur at the item, scale, and timepoint levels. Recommendations on handling of missing item data from scoring protocols will be followed. Otherwise, items will be prorated where 75% or more items for a scale are present. Mechanisms for missing data on variables and key scales will be explored and a multiple imputation model built covering the primary analysis. A sensitivity analysis will explore the impact of employing different missing data handling strategies.

### Plans to give access to the full protocol, participant-level data, and statistical code {31c}

Upon study completion, any party may apply to the Chief Investigator for access to the full protocol, participant-level data, and statistical code for academic research purposes. An information governance committee will govern data access.

## Oversight and monitoring

### Composition of the coordinating centre and trial steering committee {5d}

The TMG will include the Chief Investigator, CTRU, and key external staff members, including two individuals with acquired brain injuries from the PPI group. TMG responsibilities will include clinical set-up of the study, ongoing management, study promotion, and planning for interpretation and dissemination of results. TMG meetings will be held quarterly as a minimum. Further PPI will be provided by the trial’s PPI group, which will include individuals from Different Strokes, Stroke Association, and Headway charities.

The TSC will include an independent chairperson and multiple independent members (including a PPI group member, statistician, and person/s with clinical and trial experience). TSC meetings will take place annually at a minimum to monitor study progress and provide public, clinical, and/or professional advice to TMG members. A TSC sub-committee will review safety issues where necessary.

### Composition of the data monitoring committee, its role and reporting structure {21a}

The CTRU at the University of Leeds will be responsible for monitoring the quality and completeness of study data, in accordance with Standard Operating Procedures (SOPs) and Consolidated Standards of Reporting Trials (CONSORT) guidelines. The TSC will be responsible for reviewing clinical governance issues (in liaison with NHS Trusts, if relevant), and any concerns warranting modification or termination of the study. Decision to terminate the study will be made by the TSC and sponsor.

### Adverse event reporting and harms {22}

Adverse events will be reported if classified as a Related and Unsuspected Serious Adverse Event (RUSAE), i.e. an event that is unexpected in severity and seriousness, and suspected to be related to the study intervention. Possible examples include accidental injury resulting from workplace adaptations recommended by a RETAKE OT, and/or work accidents resulting in injury and hospital treatment.

Self-reported data on adverse events will be collected at 3, 6, and 12 months post-randomisation, or via a site notifying the CTRU or research team. Adverse events will be immediately reported to the Chief Investigator, who will take appropriate medical action, inform and send follow-up information and reports to the REC, and make necessary protocol amendments.

### Frequency and plans for auditing trial conduct {23}

Investigators will notify the CTRU if there is a breach of protocol or GCP principles likely to significantly affect participants’ safety, health, and wellbeing, or scientific value of the research.

### Plans for communicating important protocol amendments to relevant parties (e.g. trial participants, ethical committees) {25}

Important protocol amendments will be made by the Chief Investigator, following consultation with the TMG and any required approval from the REC and Research and Development departments. Amendments will be communicated to participants by the PI, and an amended Informed Consent form completed.

### Dissemination plans {31a}

Study findings will be disseminated, regardless of direction or magnitude of effect, through journal articles, conference presentations, and a peer-reviewed NIHR HTA report submitted within 14 days of study completion. Authorship decisions will be guided by journal criteria. Local collaborators will not have access to study data until publication of the main findings. Participants, study investigators, and PPI group will be informed of results via the study newsletter.

